**Figure 1 figure1:**
[figure not shown]
Study flowchart.

### Eligibility and Recruitment

Participants will be recruited from the Obstetrics and Gynecology Hospital of Fudan University, where they will receive routine antenatal care and plan to give birth. Upon admission to the LDU, trained research staff will identify eligible women through a screening process that includes reviewing medical records and conducting brief assessments. Inclusion criteria require participants to have a singleton pregnancy with cephalic presentation, to be in good maternal and fetal health at admission, to plan to undergo a trial of labor, and to have no cognitive dysfunction or communication difficulties. Women with preexisting or pregnancy-related complications, as well as those with medical indications necessitating a cesarean section, are excluded from the study.

Eligible participants will be approached by trained research staff, who provide detailed information about the study’s purpose, procedures, and potential risks and benefits. Written informed consent will be obtained from all participants before enrollment, and they will be informed of their right to withdraw from the study at any time without consequences.

### Sample Size

The sample size calculation is conducted using the formula for SWCRCTs as outlined by Hemming and Taljaard [30]. The design effect (DE) was calculated based on the meta-analysis by Johnson et al [14], which suggests that a reduction exceeding 0.7 in VAS pain scores indicates a clinically significant effect of TENS. Assuming an expected effect size of 0.7, an intraclass correlation coefficient (ICC) of 0.01, and an estimated sample size of 117 participants in each intervention group, the DE is determined to be 2.16. The total sample size is then estimated using a significance level of 0.05 and a power of 0.8, resulting in 132 participants per group. After accounting for a 10% dropout rate, the required sample size is adjusted to 147 participants per group, culminating in a total of 588 participants. This calculation is verified using PASS 15.0 software (NCSS), which confirms a power of 0.89, thus ensuring the study’s adequacy.

### Randomization and Allocation

This study uses a SWCRCT design, wherein the interventions are allocated at the cluster level, specifically based on the LDUs, rather than at the individual participant level. The randomization process is conducted by a researcher not involved in the intervention using a computer-generated random number list to determine the sequence of interventions across the 4 LDUs. The random allocation sequence is subsequently sealed in opaque envelopes, each corresponding to a specific LDU. This allocation sequence will be disclosed to the midwives in each cluster at the appropriate time. The midwives, trained to implement the intervention, will execute it according to the allocated sequence. This approach ensures allocation concealment and mitigates the risk of selection bias.

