## Methods

### Trial Design

This 12-month exploratory SWCRCT will be conducted at the Obstetrics and Gynecology Hospital of Fudan University in Shanghai, China—a specialized tertiary hospital that manages approximately 10,000 births annually across its 2 campuses. The study involves 4 parallel groups, assigned in a 1:1 ratio, each receiving 1 of 4 interventions: TENS, acupoint stimulation, a combination of TENS and acupoint stimulation, or control measures. Randomization is performed at the cluster level using computer-generated sequences to determine the staggered initiation order of interventions across 4 labor and delivery units (LDUs; LDU1, LDU2, LDU3, and LDU4). Each LDU will be assigned to deliver a single intervention for a 3-month period, followed by a transition to the next phase according to the predetermined sequence. This design ensures that each 3-month cohort will comprise unique participants, eliminating crossover exposure to multiple interventions. Participants will be selected based on predefined criteria and confirmed for inclusion before the initiation of the interventions. Figure 1 shows the overall study flow. Recruitment began on April 1, 2023, and all interventions were completed by March 29, 2024, aligning with the 12-month study window. This protocol adheres to the SPIRIT (Standard Protocol Items: Recommendations for Interventional Trials) 2013 checklist [29].

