### Blinding

A double-blind design is not feasible in this study due to the necessity for participants to provide informed consent regarding the pain relief methods administered. However, several measures are implemented to minimize potential bias. Midwives delivering the interventions will not be involved in outcome assessment or data analysis, thereby reducing both performance and detection bias. A standardized protocol will be established to ensure consistent delivery of interventions and uniformity in data collection. To minimize measurement bias, outcome assessors will be blinded to the group allocation, and participants will be instructed not to disclose which treatment intervention they receive. Data collectors, who will be independent of the intervention process, do not have access to any information regarding the intervention groups. In addition, statisticians conducting the data analysis will be blinded to group allocation and will not have access to the intervention details. Analyses will be performed according to a prespecified plan to prevent selective reporting. Regular monitoring of adherence to the protocol across the LDUs will be conducted to ensure consistency and reduce the risk of bias. To further enhance the validity and objectivity of the findings, data analysis will be independently verified by a third party to minimize any potential bias.

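### Allocation concealment holds only for the LDU sequence until it is disclosed, and blinded assessment cannot hold for the self-reported VAS and CEQ; both claims should be restated and the VAS and NPI analyses adjusted for pre-intervention factors

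*Protocol article*

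**What the plan says.** **Allocation.** In Randomization and Allocation, "the interventions are allocated at the cluster level, specifically based on the LDUs, rather than at the individual participant level". The sequence is computer-generated and sealed in one opaque envelope per LDU. Then: "This allocation sequence will be disclosed to the midwives in each cluster at the appropriate time". The section concludes: "This approach ensures allocation concealment and mitigates the risk of selection bias".

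**Enrollment.** Trial Design states: "Each LDU will be assigned to deliver a single intervention for a 3-month period". It adds: "Participants will be selected based on predefined criteria and confirmed for inclusion before the initiation of the interventions". Eligibility and Recruitment places screening inside the unit: "Upon admission to the LDU, trained research staff will identify eligible women through a screening process". The same research staff then explain the study and take consent.

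**Blinding.** The Blinding section concedes that double-blinding is not feasible "due to the necessity for participants to provide informed consent regarding the pain relief methods administered". It nevertheless states that "outcome assessors will be blinded to the group allocation, and participants will be instructed not to disclose which treatment intervention they receive", and that data collectors have no information on the groups. Statisticians are also to be blinded.

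**Outcome and analysis.** The primary outcome is a 0 to 10 VAS recorded half-hourly in labor. The CEQ is completed after delivery, and the other secondary outcomes are extracted from records. Statistical Analysis names ANOVA, Kruskal-Wallis and *t* tests for continuous outcomes, with no covariate.

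**The concern.** In a cluster trial, concealing the order in which units change intervention and concealing the arm a given woman will enter are different things. Envelopes per LDU achieve the first. Once a 3-month period is running, every later woman in that unit has a known arm, so who is approached and who agrees can depend on it. The article claims the stronger protection from the weaker device.

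The blinding claim has a similar gap. The person who rates the primary outcome knows her treatment, and the treatment is visible to whoever writes the score down.

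At stake is how much certainty a reader attaches to the result. A subjective, open-label primary outcome would be credited with concealment and blinded assessment. If enrollment did differ by arm, the tests named would carry the difference into the VAS and NPI comparisons.

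**Working it through.** This is mainly a comparison of sections. The arithmetic at the end only gives a sense of scale.

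**1. Concealment.**
- What is concealed: the sequence for each LDU (Randomization and Allocation).
- Until when: disclosure to that unit's midwives, at a time not further specified.
- How long one arm then runs: 3 months (Trial Design).
- When women are identified: after admission to the unit (Eligibility and Recruitment).
- What women know: the pain relief method, since the consent concerns it (Blinding).

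Each woman is thus screened and consented after her unit's arm has been fixed, and she consents knowing the method. Confirming inclusion before the intervention starts does not change this, because that refers to the start of her own treatment and not to the setting of the LDU's allocation.

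**2. Blinding, outcome by outcome.**

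| Outcome | Who reports it | Can blinding hold? |
|---|---|---|
| VAS (primary) | The woman, in labor | No. She is unblinded, and Table 1 has electrodes on hand, forearm and back, taped ear seeds, or massage in use through the same period |
| CEQ | The woman, after delivery | No |
| Record-extracted outcomes | Staff not providing care | Yes, for extraction |
| Statistical analysis | Blinded statisticians | Yes |

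Asking women not to disclose their treatment cannot hide what is visible at the bedside. With one arm per unit at a time, ward and date also identify the arm to anyone who knows the schedule.

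**3. First VAS as a covariate.** VAS recording starts with the onset of labor pain. Table 1 starts each technique at the onset of contractions. The first score may therefore fall after treatment has begun, so it is not clearly a baseline value.

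**4. Scale (illustration only).** Inputs from the plan: 147 women per group, alpha 0.05 (taken as two-sided). Assumed, because the documents give neither: the SD and an imbalance *b* in expected VAS between two arms. Assume no true effect and independent observations.

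SE = SD × √(2/147). Rejection rate = 1 − Φ(1.96 − *b*/SE) + Φ(−1.96 − *b*/SE).

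Example: SD 2.0 gives SE = 2.0 × 0.1166 = 0.233. With *b* = 0.2, *b*/SE = 0.857 and the rate is 13.8%.

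| *b* (VAS points) | SD 1.38 | SD 2.0 | SD 2.5 |
|---|---|---|---|
| 0 | 5.0% | 5.0% | 5.0% |
| 0.1 | 9.5% | 7.1% | 6.4% |
| 0.2 | 23.7% | 13.8% | 10.5% |
| 0.35 | 58.5% | 32.3% | 22.5% |

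The SD of 1.38 is the one that the plan's own numbers imply if 0.7 is in VAS points and the test is two-sided: 132/2.16 ≈ 61 per group, and 0.7 × √(61/2)/(1.960 + 0.842) = 1.38. The table says nothing about which *b*, if any, is present.

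**The case against.** **Recruiter knowledge is inferred.** Only midwives are named as receiving the sequence, and screening is done by research staff. This stands. A ward-wide intervention and a consent that covers the method make masked recruitment implausible, but the article does not say what recruiters knew. A reader might infer that concealment was wholly absent or that selection took place. The documents support neither: the sequence was concealed until disclosure, and no enrollment data by arm are shown.

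**The lack of blinding is already conceded.** The article says that double-blinding is not feasible, and Limitations acknowledges that the VAS is subjective. This is fair, and the women's knowledge is not hidden. But the same Blinding section still asserts blinded assessors and uninformed data collectors without exempting the VAS. A reader might go further and infer that all blinding fails. It need not: extraction by staff outside care and blinded statistical analysis are both feasible.

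**Covariates may be in a plan not shown.** The Blinding section refers to a prespecified plan, and a condensed article need not list covariates. This stands, so the missing list is not itself a fault. The tests that are named are unadjusted, however, and naming an adjusted model is a worthwhile improvement.

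**Adjustment does not cure selection on preference.** Correct. If women set on an early epidural decline one arm more often, parity or dilation will not capture that.

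**Each LDU delivers every intervention.** Stable differences in case mix between units are therefore not the source of imbalance. The remaining route is enrollment that depends on the current intervention.

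**Size.** It is tempting to set the 600 women enrolled against about 10,000 births a year and read selectivity from it. That denominator covers both campuses and ineligible women, and the target was 588 in any case. Nor do the documents support turning an assumed parity imbalance into VAS points, since they give neither the imbalance nor the difference in pain by parity.

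**Conclusion.** The concern holds as a matter of overstated safeguards. The concealment statement is true of the LDU sequence up to disclosure and does not extend to enrollment. The assessor-blinding statement cannot be true of the VAS or the CEQ, and it can be true of record extraction and statistical analysis.

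The consequence is a risk of selection at enrollment and of expectation influencing a self-reported primary outcome. Neither is shown to have occurred, and no bias estimate follows from the documents. The false-positive rates above depend entirely on the assumed SD and imbalance, and show only that a shift well below the 0.7-point target would matter to an unadjusted test.

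The conclusion rests on two readings: that consent covers the method in use in that unit, and that recruiters were not masked, since no masking is described. If recruiters were in fact masked, the enrollment point weakens to the women's own knowledge at consent. The blinding point is unaffected.

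**What to change.** 1. Replace the concealment sentence with: *LDU-level sequence concealed until disclosed; women recruited after the LDU's allocation was set.* State what the recruiting staff knew at screening and consent.
2. Describe the VAS and CEQ as unblinded self-reports, and limit the blinding claim to record extraction and statistical analysis.
3. Report women screened, eligible and consenting, with baseline factors, by LDU and 3-month period.
4. For the VAS and NPI, replace the unadjusted tests with a model that includes pre-intervention factors taken from the records: parity, cervical dilation at enrollment, and spontaneous or induced onset. Fix the list before group comparisons are seen. Use the first VAS only where it was recorded before the intervention began.
5. State that adjustment removes measured imbalance only, and not selection on preference.

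**Cost.** Enrollment and data collection are complete, so recruitment cannot change, but analysis was still in progress at publication. Items 1, 2 and 5 are wording. Items 3 and 4 need a few record fields and screening counts, if these were kept. The price is a less favorable description of the trial's protection against bias.

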### Intervention

A literature analysis method is used to systematically search for relevant studies across multiple databases, including the Cochrane Library, JBI Evidence-Based Nursing Database, Medline, Embase, WanFang Data, SinoMed, CNKI, and VIP. This search uses keywords related to TENS, auricular seed acupressure, and acupressure specifically for women undergoing a trial of labor. A total of 27 studies on TENS, 30 studies on auricular seed acupressure, and 41 studies on acupressure were retrieved. Content analysis is subsequently applied to extract key information from the selected literature. The research team will conduct content extraction, analysis, and synthesis on relevant topics to draft an initial intervention plan for labor pain relief using TENS combined with acupoint stimulation for women in the trial of labor. Based on this draft, expert consultations will be organized to revise the plan, ultimately resulting in the final version of the intervention protocol.

Before the implementation of the project, the midwives at the 4 LDUs will participate in a 1-week training course led by researchers qualified in TCM nursing. The course will cover the operational procedures and assessment of the 3 nonpharmacological pain relief techniques. Competency will be evaluated using a percentage-based scoring system that assesses key aspects such as knowledge of protocols, practical skills, and communication effectiveness. Midwives who achieve a score of 80 or higher will pass the assessment and receive a TCM-based labor pain relief technique certification from the study institution. This certification ensures that all relevant personnel are proficient in the standardized implementation of these techniques before the intervention.

Table 1 shows detailed descriptions of the 3 intervention techniques. These interventions will be administered to participants during labor progression, spanning from the initial onset of contractions to final delivery. All interventions will be individualized according to each participant’s unique labor progression and birthing context while being strictly confined to a single care episode to ensure protocol consistency. To mitigate cross-contamination risks among study groups, designated cluster units (LDU wards) will maintain geographic separation and administrative independence.

Participant adherence to the interventions will be rigorously monitored throughout the study. The intervention protocol will initiate upon the onset of regular contractions and be suspended during intercontraction intervals. During these pauses, midwives will assess maternal comfort levels and dynamically adjust interventions in real time based on participant feedback. For the acupoint stimulation group, adherence will be ensured through direct observation by trained midwives, who will administer massage techniques and maintain continuous stimulation at predefined acupoints. Adherence metrics, including duration, frequency, and intensity of each intervention session, will be recorded using a standardized log sheet. Maternal willingness and comfort will serve as primary adherence indicators, ensuring that interventions remain tolerable and beneficial throughout labor. Participants retain the autonomy to modify or discontinue the intervention at any time, with all adjustments documented for analysis. Regular feedback will be collected through brief interviews and comfort assessments, with findings integrated to refine intervention delivery while safeguarding maternal well-being.

To ensure data accuracy and protocol fidelity, a comprehensive quality assurance framework will be implemented, including (1) regular oversight by the research team, involving scheduled audits to assess adherence to intervention protocols; (2) mandatory use of standardized checklists by midwives to systematically verify and document each procedural step; and (3) prompt documentation and analysis of protocol deviations, with root-cause investigations conducted to address discrepancies. In case of identified nonadherence, targeted retraining sessions will be provided to reinforce proper procedures and ensure understanding of the protocol. These measures are designed to maximize intervention fidelity, ensure methodological rigor, and uphold the integrity of the study.

**Table 1 table1:** Description of intervention protocols.

Intervention types			Detailed descriptions
Low-frequency pulsed electrotherapy or TENS^a^ (T)			Preprocedure preparation: The midwife will prepare the TENS device, electrodes, and connecting wires. The laboring woman will be positioned comfortably, and the skin will be cleansed with warm water. Procedure: Electrodes will be placed on the Hegu (LI4) point, Neiguan (PC6) point, T10-L1, and S2-S4 (Figure 2). The device will be set to alternate between frequencies of 2 Hz and 100 Hz every 6 seconds, with pulse widths of 0.6 ms for 2 Hz and 0.2 ms for 100 Hz. The intensity will be gradually increased from low to high based on the laboring woman's feedback until the optimal stimulation level is achieved. Typically, the intensity for channel 1 (Hegu and Neiguan points) will be set between 6 and 15 mA, while for channel 2 (T10-L1 and S2-S4), it will range from 6 to 40 mA. The midwife will instruct the laboring woman on how to adjust the intensity, empowering her to modify the settings according to her comfort level. Timing of application: TENS therapy will commence at the onset of contractions, with intensity increased during contractions and decreased during periods of relief. This therapy will continue as tolerated until the delivery of the placental. Postprocedure care: Upon completion of the treatment, the device will be turned off, electrodes will be removed, and the skin will be inspected for any signs of irritation. The area will be cleansed to ensure hygiene is maintained.
**Acupoint stimulation (A)**			
	Auricular seed acupressure	Preprocedure preparation: The midwife will prepare a treatment tray containing a kidney dish, 75% alcohol swabs, and vaccaria seeds (Wang-Bu-Liu-Xing) with adhesive tape, tweezers, and a probe. The laboring woman will be positioned comfortably in a sitting, supine, or lateral position to ensure full exposure of the ear. Procedure: The midwife will stabilize the auricle and use a probe to identify the positive reaction points at the bilateral Uterus (TF2), ShenMen (TF4), Endocrine (CO18), Sympathesis (AH6a), and Subcortex (AT4) points (Figure 3). After disinfecting the ear with an alcohol swab, the midwife will apply vaccaria seeds with adhesive tape onto the selected acupoints and press them for 1-2 min per side to enhance stimulation. Timing of application: The procedure will be performed at the onset of contractions. The seeds should be pressed for 1-2 min per contraction or as tolerated until placental delivery. Postprocedure care: The seeds can remain in place for up to 1-2 days post delivery to alleviate uterine contraction pain. If the laboring woman experiences discomfort or requests removal, the procedure should be terminated immediately. After removal, the midwife should clean the auricle, ensure patient comfort, and adjust clothing and bedding.	
	Acupressure	Preprocedure preparation: The midwife should encourage the woman in labor to empty her bladder and bowels, ensure a comfortable position, and maintain warmth. Procedure: During the latent phase of labor, due to the slow cervical dilation, abdominal pain tends to concentrate around the GuanYuan (CV4) point. The midwife can provide a massage using the palm of her right hand in a clockwise direction. Simultaneously, the left thumb can be used to apply pressure to the HeGu (LI4), NeiGuan (PC6), and KunLun (BL60) points (Figure 4). In the active phase of labor, the woman will be advised to adopt a left lateral position with the ZhongJi (RN3) point as the center. Pillows and cushions can be used to support the woman’s head and upper thigh. The midwife will use clockwise abdominal massage and apply pressure to the HeGu (LI4), SanYinJiao (SP6), TaiChong (LR3), and ZuSanLi (ST36) points. For back pain, focusing on the CiLiao (BL32) points, the woman should lean forward against a wall or support herself on the edge of the bed to minimize fetal weight on the spine. The midwife will provide a massage to the lumbar and sacral regions, as well as the back, including the ShenYu (BL23) points, and perform a circular massage around the buttocks with the HuanTiao (GB30) point as the center (Figure 5). Timing of application: Acupoint massage should begin at the onset of contractions and be paused during periods of relief. It may continue as tolerated until placental delivery. Postprocedure care: If the laboring woman experiences discomfort or requests termination, the procedure should be stopped immediately. The midwife should cleanse the skin, adjust the woman’s clothing, and ensure her comfort.	
Combination of TENS and acupoint stimulation (T&A)			Preprocedure preparation: The midwife will prepare all necessary tools, including TENS equipment, Vaccaria seeds, alcohol swabs, tweezers, and a probe. The laboring woman will be positioned comfortably to ensure relaxation. Procedure: Initially, the midwife will apply auricular acupressure and place the TENS electrodes. During contractions, the laboring woman will be encouraged to massage the auricular acupoints, adjust the TENS intensity, and receive an acupoint massage. When experiencing contraction relief, the acupoint massage should be paused, allowing the laboring woman to adjust the TENS settings as needed. This intervention may continue as tolerated until placental delivery. Timing of application: This combined approach may be sustained as tolerated until placental delivery. Postprocedure care: If discomfort occurs, adjustments to the technique should be made, or it should be discontinued. The midwife should turn off and remove the TENS device, inspect the skin, and cleanse the area. Auricular acupressure may be continued for 1-2 days post delivery unless discomfort arises.

^a^TENS: transcutaneous electrical nerve stimulation.

